In Wales, following detection of PCD (5-9.9mm) at the 18–20 week ultrasound scan, a follow-up scan is offered

between 28 – 32 weeks, and if the dilatation is >7 - 8 mm (depending on local protocols) a scan is indicated in

the post-natal period. Congenital hydronephrosis (dilatation > 10mm) detected at the post-natal scan could

indicate VUR and/or obstruction, requiring treatment with prophylactic antibiotics or surgery. Preliminary analysis of data from the Congenital Anomaly Registry and Information Service for Wales (CARIS) showed that 58% of babies with PCD 5-9.9mm detected on antenatal ultrasound scan were followed-up at birth, and of these cases, 28% of babies had congenital hydronephrosis (PCD > 10mm). 80% of babies with congenital hydronephrosis detected on antenatal ultrasound scan (>10mm) were followed up at birth and 77% of these babies had this diagnosis confirmed on post-natal scan. Although congenital hydronephrosis is defined in Europe using the measurement of at least 10mm, local protocols indicate some hospitals use a measurement of at least 7mm to define and treat cases. There are no data on the degree of progression as determined by change in measurement between antenatal or post-natal scan or the influence of measurement error, and no information about the correlation between size of PCD and urinary tract morbidity, so it is not known whether or not the 10mm cut-off to define congenital hydronephrosis is appropriate or not.

One study set in the Netherlands investigated the incidence of urinary tract infections at age 5 – 6 years and

found no difference between babies with and without PCD (5-9.9mm).^20^ However the diagnosis of urinary tract

infection was solely by parental report with no medical diagnosis and so the question remains unanswered. No

study has compared hospital admissions for renal causes between babies with and without PCD.

The natural history and evidence for any association between PCD (5-10mm) and urinary tract outcomes in

childhood needs to be established in order to define clinical guidelines and requirements for subsequent management of pregnancy and postnatal follow-up for this condition.

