**Outcome measures**

1. Proportion of children with any renal hospital admissions (defined by ICD-10 codes N00–N99, Q60-Q64

recorded in the primary or secondary coding position) and/or linked procedures (OPCS-4). We will define the

codes for renal ultrasound scan, micturating cystourethrogram (MCUG), Dimercaptosuccinic (DMSA) scan and

surgery for urinary tract obstruction using the Classification of interventions and procedures (OPCS-4) which is

used for the coding of operations, procedures and interventions performed in the NHS.

2. Incidence of urinary tract infections and repeat infections in children under age five diagnosed in primary care. These will be defined using Read codes for clinical activity and drug prescriptions relating to primary care

diagnosis, investigation and treatment of urinary tract infection. Read codes version 2.0 is available from the

Technology Reference data Update Distribution (TRUD) website, Department of Health, England.

3. Time to first hospital admission for renal conditions in children under age 5 defined by ICD10 codes N00 –

N99 and Q60 – 64 in the primary and secondary coding position. We will code the children who have migrated

out of Wales or who die so that we can take this censoring into account in the analysis.

4. Number of hospital admissions for renal conditions and urinary tract infections (as defined above) during

childhood, over a maximum follow-up period of five years.

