**Statistical Analysis**

We will define three groups for analysis:

1. Babies with no markers and no major congenital malformations

2. Babies with a renal marker (PCD, 5 - 9.9mm) on the 18-20 week antenatal ultrasound scan

3. Babies with congenital hydronephrosis (>10mm) on the 18-20 week antenatal ultrasound scan

For groups 2 and 3 we will define three subgroups according to diagnosis at birth:

(a) no pathology (<7 mm)

(b) pelvicalyceal dilatation (7-9.9mm)

(c) confirmed congenital hydronephrosis (>10mm).

We will describe the natural history for babies in groups 2 and 3 including the detail of measurements of PCD at follow-up scans after birth using data from CARIS. We will describe the proportion of babies in sub-groups a, b and c, the proportion of children in these groups with any renal hospital admissions and/or linked procedures, and the incidence of urinary tract infections diagnosed in primary care.

For each baby we will define the length of follow-up and person-years at risk during the five-year study period,

accounting for censoring by death or migration. We will estimate and compare the proportion of hospital

admissions and the person-year incidence of urinary tract infections between groups 1, 2 and 3 according to

maternal age, parity, quintile of Townsend deprivation score quintile, gestational age, sex, and breast-feeding.

We will use time to event Cox’s regression analysis for the first admission to hospital for renal disease to obtain crude and adjusted hazard ratios for groups 2 and 3 as defined above compared to group 1; the adjustments will be for maternal age, parity, social deprivation, gestation, sex, birth-weight and breast-feeding.

We will model the number of urinary tract infections and hospital admissions for renal conditions separately using a negative binomial or Poisson model, depending on whether or not there is over-dispersion, allowing for the varying periods of time at risk for the children in the cohort, adjusting for the factors listed above.

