**Sample size calculations**

Prelimiunary data from the PEDW dataset for the period 1998 to 2008 linked to 329,000 live births from WECC,

showed that there was a 1% chance of a renal admission before the first birthday, increasing to 2.8% by the

fourth birthday and 3.3% by the fifth birthday. The most common reasons for renal admission in children under 5 were urinary tract infection (ICD10 N39.0), non-specific renal condition (ICD10 39.9) and hydronephrosis (ICD10 N13.3). Admissions were more common in boys than girls, with a relative risk ratio of approximately 1.6. We will compare the rates of renal admissions between the 148 children with PCD and those without a marker. There will be 80% power for detecting a hazard ratio of at least 6.2 in admissions by the first birthday and for detecting a hazard ratio of 3.5 by the fourth birthday. Whilst these are large effect-sizes this study presents a unique opportunity to describe the natural histrory of PCD.

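### The renal-admission outcome accepts hydronephrosis and urinary-anomaly codes in any position, so the antenatal label alone can inflate the hazard ratio and admission counts; add a restricted analysis

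*Protocol*

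**What the plan says.** Protocol, Outcome measures. Outcome 1 is the proportion of children with an admission coded N00–N99 or Q60–Q64, "recorded in the primary or secondary coding position) and/or linked procedures (OPCS-4"; the procedures to be coded are "codes for renal ultrasound scan, micturating cystourethrogram (MCUG), Dimercaptosuccinic (DMSA) scan and" surgery for obstruction. Outcome 3, time to first renal admission, uses "N99 and Q60 – 64 in the primary and secondary coding position" and names no procedures. Outcome 4 is the "Number of hospital admissions for renal conditions and urinary tract infections (as defined above", so it inherits the same definition.

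Protocol, Statistical Analysis. The Cox model is a "regression analysis for the first admission to hospital for renal disease to obtain crude and adjusted hazard ratios for groups 2 and 3" against group 1. Group 3 is defined by congenital hydronephrosis on the antenatal scan, and confirmed congenital hydronephrosis at birth is a subgroup of both group 2 and group 3. Group 1 has neither markers nor major malformations; no malformation exclusion is stated for groups 2 and 3.

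Protocol, Sample size calculations. The commonest renal admission reasons under age 5 are given as "urinary tract infection (ICD10 N39.0), non-specific renal condition (ICD10 39.9) and hydronephrosis (ICD10 N13.3"), so hydronephrosis is a counted event.

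Protocol, Background. "In Wales, following detection of PCD (5-9.9mm) at the 18–20 week ultrasound scan, a follow-up scan is offered" at 28–32 weeks, with a postnatal scan above a local threshold of 7–8 mm. In preliminary registry data, "58% of babies with PCD 5-9.9mm detected on antenatal ultrasound scan were followed-up at birth, and of these cases, 28% of babies" had congenital hydronephrosis.

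**The concern.** The aim is to learn whether babies with the marker have more urinary infections or more admissions for kidney problems. The event definition does not separate an admission *for* a kidney problem from an admission *of* a child already known to have a dilated kidney.

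The chance of carrying the code differs between groups by design:

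- Babies in groups 2 and 3 have a recorded finding and a pathway to further scanning. Group 1 babies have neither.
- Group 1 is cleared of major malformations, yet congenital urinary anomaly codes (Q60–Q64) count as events. The reference group therefore loses some potential events by definition.
- A secondary-position code is enough. A birth stay, or an admission for an unrelated illness, counts once the finding is noted on it.

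The planned covariates (maternal age, parity, deprivation, gestation, sex, birth weight, breast-feeding) do not measure labelling and cannot remove it. A raised hazard ratio could then be read as renal morbidity in guidelines and parent counselling, which the protocol names as uses of the results, when part of it reflects coding.

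**Working it through.** **Inputs, all from the protocol.** Background: 58% of PCD babies followed up at birth, 28% of those with hydronephrosis; for antenatal hydronephrosis, 80% and 77%. Sample size calculations: 148 PCD children; risk of renal admission 1% by the first birthday and 2.8% by the fourth; hazard ratios of 6.2 and 3.5 detectable with 80% power.

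**The plan's own figures.** The protocol states neither the comparator size nor the method. Using Schoenfeld's formula with two-sided alpha 0.05 (assumed), 148 against 592 children (1:4) gives power of 80.3% at 6.2 and 79.1% at 3.5, so both figures can be reproduced. Against about 20,960 children the same formula gives 61% and 73%. That mismatch is a separate matter; 6.2 and 3.5 serve here only as the plan's own yardstick.

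**Labelled babies in group 2.** 0.58 × 0.28 = 0.1624; 0.1624 × 148 ≈ 24.

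**Apparent hazard ratio when the true one is 1.** Let p0 be the background risk and f the share of the 24 whose code appears on at least one admission by that age. The documents do not give f, so a range is shown.

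- p1 = 1 − (1 − p0)(1 − 0.1624 f)
- apparent HR = ln(1 − p1) / ln(1 − p0)

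Example: p0 = 0.028, f = 0.5. p1 = 1 − 0.972 × 0.9188 = 0.1069; HR = ln(0.8931)/ln(0.972) = 4.0.

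| f | children coded | HR by 1st birthday (p0 = 1%) | HR by 4th birthday (p0 = 2.8%) |
|---|---|---|---|
| 10% | 2.4 | 2.6 | 1.6 |
| 25% | 6.0 | 5.1 | 2.5 |
| 50% | 12.0 | 9.4 | 4.0 |
| 100% | 24.0 | 18.6 | 7.2 |
| *stated detectable* | | *6.2* | *3.5* |

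**How many label-only children reach the stated values?** Setting the apparent HR to h requires a label-only share of 1 − (1 − p0)^(h − 1).

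- First birthday: 1 − 0.99^5.2 = 0.0509; × 148 = 7.5 children, or 31% of the 24.
- Fourth birthday: 1 − 0.972^2.5 = 0.0685; × 148 = 10.1 children, or 42% of the 24.

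The numbers are small because the background is small: 148 × 0.028 = 4.1 expected events by the fourth birthday, and 148 × 0.01 = 1.5 by the first.

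**Group 3.** 0.80 × 0.77 = 0.616 have the diagnosis confirmed after birth. The label is therefore commoner than in group 2 and coincides with the group definition.

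**Where imaging enters.** Renal ultrasound, MCUG and DMSA are named only in outcome 1. Outcomes 3 and 4, and hence the Cox and count models for admissions, rest on ICD-10 codes. A scan enters them only if it takes place in an admission that also carries an N or Q code.

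**The case against.** The strongest reply is that hydronephrosis after birth is not the exposure. Group 2 is defined by 5–9.9 mm at 18–20 weeks; more than 10 mm after birth is persistence or progression. The Background says it may indicate reflux or obstruction needing treatment, and natural history is a stated purpose. This stands. For group 2 the code is not simply the exposure counted again, and some of the 24 will have genuine renal admissions. The identity is close only for group 3.

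A reader might also infer that surveillance scans drive the Cox hazard ratio. The documents do not support that: procedures belong to outcome 1, the first follow-up scan is antenatal, and nothing says postnatal scans are admissions. Nor do they support saying that a large hazard ratio *will* arise. The coded share is unknown, and at 10% the fourth-birthday value is only 1.6.

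Two partial safeguards exist. Primary-care urinary infection is a separate outcome with its own codes. Admissions and procedures will also be described by birth-status subgroup, so an excess confined to confirmed hydronephrosis would be visible. But the first relies on practices covering about 50% of Wales when the protocol was written, and the second is descriptive. Neither corrects the hazard ratio.

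A detailed code list and a birth-stay rule could sit in a SAP that is not shown, and their absence here is not itself a fault. The code ranges and the acceptance of secondary positions, however, are fixed in the protocol.

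**Conclusion.** The concern holds in a limited form. As written, the admission hazard ratio and counts for groups 2 and 3 against group 1 are open to inflation by differential labelling, and the protocol text shown has no restricted analysis that would reveal it. In group 2, about 8 label-only children of 148 by the first birthday, or about 10 by the fourth, would produce the hazard ratios the study says it can detect.

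This rests on four assumptions:

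- The preliminary registry percentages carry over to the 148 study children.
- The background risks apply to group 1.
- The code's presence is independent of background renal admissions.
- Outcome 3's wording on coding positions means either position, as in outcome 1.

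The calculation also treats every coded child as having no real renal illness, so its figures are illustrative and at the upper end. It does not follow that the study cannot answer its question, or that the broad outcome should be dropped. Dropping it would also discard true admissions for obstruction or reflux. A prespecified companion analysis is enough.

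**What to change.** Keep the broad outcome and prespecify beside it:

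1. A restricted Cox and count analysis that excludes the birth admission and counts only admissions with a renal or urinary code in the primary position. Hydronephrosis or anomaly codes qualify only when they are the primary reason for admission or accompany urinary tract surgery.
2. A further version limited to urinary tract infection in the primary position.
3. In outcome 1, imaging-only contacts (renal ultrasound, MCUG, DMSA) reported separately from admissions and from surgery.
4. A statement that any conclusion about excess renal morbidity will rest on agreement between the broad and restricted results.

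The cost is protocol wording and a code list, with no new data. The restricted analysis will have fewer events and so a larger detectable hazard ratio than the stated 6.2 and 3.5. The documents do not give the split of codes by position, so that loss cannot be quantified here.

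### The primary-care UTI definition admits prescription and investigation codes without requiring a diagnosis, so prophylactic antibiotics could be counted as infections almost only in the dilatation groups

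*Protocol*

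**What the plan says.** The outcome is introduced as "Incidence of urinary tract infections and repeat infections in children under age five diagnosed in primary care". The next sentence says how it will be measured: "These will be defined using Read codes for clinical activity and drug prescriptions relating to primary care", continuing "diagnosis, investigation and treatment of urinary tract infection". Diagnosis, investigation and prescribing codes are all named as parts of the definition. Nothing says whether a diagnosis code is necessary, whether a prescription or test can stand alone, what separates one episode from a repeat, or how preventive prescriptions are treated.

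The Background says that dilatation above 10 mm on the post-natal scan could "indicate VUR and/or obstruction, requiring treatment with prophylactic antibiotics or surgery". It adds that some hospitals apply a lower threshold of 7 mm when defining and treating cases.

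Under Statistical Analysis, groups 2 (PCD 5-9.9 mm) and 3 (hydronephrosis above 10 mm) are compared with group 1, which has no marker and no major malformation. The comparisons cover person-year UTI incidence and a Poisson or negative binomial model of UTI counts.

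**The concern.** A prescription to prevent UTI and one to treat it can look alike in a coded record. If a prescription code can contribute to a UTI episode without a diagnosis, the preventive ones may be counted. The reason for giving them, hydronephrosis found after birth, is largely confined to groups 2 and 3. The resulting misclassification depends on exposure and pushes the comparison towards an excess of UTI in those groups.

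The listed adjustment factors (maternal, socioeconomic, perinatal and feeding variables) cannot remove this, because none of them carries information on why an antibiotic was prescribed. Repeat infections and the count model are the most exposed, since prophylaxis may be prescribed more than once.

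UTI is one of the two outcomes named in the study's aim. The Background also faults an earlier Netherlands follow-up study because its UTIs came from parental report without a medical diagnosis. An episode resting on a prescription alone would also lack one, and here the error would follow exposure.

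**Working it through.** The Protocol gives no figure for UTI frequency, prophylaxis uptake or prescription counts, so there is no stated result to reproduce. The check sizes the group at risk of miscounting and then shows what miscounting would do under labelled assumptions.

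**Inputs from the Protocol**
- Group 2, Background: "58% of babies with PCD 5-9.9mm detected on antenatal ultrasound scan were followed-up at birth, and of these cases, 28% of babies had" hydronephrosis.
- Group 3, Background: "80% of babies with congenital hydronephrosis detected on antenatal ultrasound scan (>10mm) were followed up at birth and 77% of these babies" had it confirmed.
- Number with PCD, Sample size calculations: 148. The Background's 150 gives the same rounded result.
- Maximum follow-up: five years. General-practice coverage: about 50% (Data sources).

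**Share with known post-natal hydronephrosis**
- Group 2: 0.58 × 0.28 = 0.162, and 148 × 0.1624 = 24.0 babies.
- Group 3: 0.80 × 0.77 = 0.616. The group's size is not given, so no count follows.

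**Illustration 1: false UTIs per person-year.** Assume that all 24 babies receive prophylaxis, that everyone is followed for five years, and that one prescription each is miscounted.
- Group 2 person-years: 148 × 5 = 740.
- Added rate: 24 / 740 = 0.0324, about 32 per 1,000 person-years.
- At 50% practice coverage unrelated to prophylaxis: 12 / 370 = 0.0324. The rate is unchanged, but about half as many affected children are observed.
- Group 3 on the same assumptions: 0.616 / 5 = 0.123, about 123 per 1,000 person-years.

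**Illustration 2: apparent risk ratio when there is no true difference.** Let u be the true UTI risk in every group, q the share above, and f the fraction of those children who are counted as UTI cases through prophylaxis alone. Assume no such error in group 1. Then

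apparent RR = [u + (1 − u) × q × f] / u.

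Neither u nor f is in the documents. The assumed ranges are u = 3% to 10% and f = 25% to 100%.

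| u | f | Group 2 | Group 3 |
|---|---|---|---|
| 10% | 25% | 1.37 | 2.39 |
| 5% | 50% | 2.54 | 6.85 |
| 3% | 100% | 6.25 | 20.92 |

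For the middle row, group 2: [0.05 + 0.95 × 0.1624 × 0.5] / 0.05 = 0.1271 / 0.05 = 2.54.

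With f = 0, as when prescriptions cannot count alone, the ratio is 1.0 in both groups.

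**The case against.** The strongest reply is that the Protocol limits the outcome to infections diagnosed in primary care and the codes to those relating to UTI. Prophylaxis is not treatment of a UTI, the code types are joined by *and*, and no sentence says that one prescription is enough. The combination rule could also sit in an analysis plan or code list that is not at hand.

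Much of this stands. A reader might infer that prophylaxis **will** be counted, but the text supports only that it **could** be. It does not dispose of the point. The diagnosis wording states what is to be captured, while the following sentence sets the measurement, names prescriptions as a component and excludes nothing. The Protocol has thus already chosen the ingredients that create the risk.

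Other stronger readings also fail:
- *Surveillance imaging inflates UTI.* The definition of outcome 1 covers "codes for renal ultrasound scan, micturating cystourethrogram (MCUG), Dimercaptosuccinic (DMSA) scan and" obstruction surgery, all under OPCS-4 rather than the Read-coded UTI outcome. Only primary-care tests such as urine tests could matter, and the Protocol does not describe these as surveillance.
- *All babies with dilatation receive prophylaxis.* The Background ties it conditionally to post-natal hydronephrosis, with surgery as an alternative. The 7 mm practice in some hospitals could widen the affected share by an unstated amount.
- *Much larger false rates are established.* Four or twelve miscounted prescriptions per child would give 24 × 4 / 740 = 130 or 24 × 12 / 740 = 389 per 1,000 person-years. That requires every prescription to count as a new episode, which the Protocol does not say.
- *The admission results are compromised.* The only power statement concerns admissions ("We will compare the rates of renal admissions between the 148 children with PCD and those without a marker"). The admission proportion and time to first admission do not use the Read-code definition.

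**Conclusion.** The concern holds as a risk left open by the definition. Prescription and investigation codes are part of the UTI outcome, no diagnosis code is required, and the Protocol itself expects prophylaxis in some exposed babies. Any miscounting would fall almost only on groups 2 and 3 and would bias the UTI incidence, repeat-infection and count-model comparisons away from the null.

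The 16% and 62% shares follow from the Protocol's preliminary registry figures and count babies not followed up at birth as having no known hydronephrosis. The 32 per 1,000 person-years is hypothetical: it assumes full uptake, one miscounted prescription each and complete five-year follow-up. The risk ratios rest on assumed u and f. They show that the error could by itself produce an apparent association, not that it will.

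**What to change.** In outcome 2, state for the main analysis that:
1. a UTI episode requires a UTI diagnosis code or, where recorded, a positive culture;
2. prescription and primary-care urine-test codes may only corroborate a diagnosis within a stated window, and never count alone;
3. prophylactic or repeat antibiotic series are reported as a separate descriptive variable by group;
4. the broad definition is kept as a sensitivity analysis.

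Settle this before linked outcomes are seen, so that the definition cannot be chosen in the light of group differences.

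The cost is wording and a code list, with no new data source. The downside is that UTIs treated without a diagnosis code are missed. That loss need not be equal across groups, because closer follow-up may also change how often diagnoses and cultures are recorded. Comparing the narrow and broad definitions would show how far the result depends on the choice.
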